# A tailored counseling and home-based rehabilitation program to increase physical activity and improve mobility among community-dwelling older people after hospitalization: protocol of a randomized controlled trial

**DOI:** 10.1186/s12891-017-1825-5

**Published:** 2017-11-21

**Keywords:** Physical activity, Sedentary behavior, Rehabilitation, Clinical trial, Mobility, Aging, Musculoskeletal, Injury

## Abstract

**Background:**

Physical activity (PA) decreases during hospitalization. In particular, the amount of PA engaged in by older people who are hospitalized following musculoskeletal injury is likely to be limited for months after discharge home. Given the importance of an active lifestyle for their recovery and the prevention of future adverse outcomes, there is clearly a need for interventions to increase PA. This article describes the protocol of a randomized controlled trial set up to investigate the effects of a physical activity oriented home rehabilitation program (ProPA) on PA and the restoration of mobility in community-dwelling older people.

**Methods:**

Men and women aged 60 years or older hospitalized due to a musculoskeletal injury or disorder in the back or lower limbs are recruited. After discharge from hospital to home, participants are randomized into a six-month ProPA program or a standard care (control) group. The ProPA program consists of a motivational interview, goal attainment process, guidance for safe walking, a progressive home exercise program and physical activity counseling. In addition, frail participants who are not able to go outdoors alone receive support from volunteers.

Primary outcomes are PA measured using a 3-dimentional accelerometer, and mobility assessed by the Short Physical Performance Battery and self-reports. Secondary outcomes are life space mobility, participation restriction, fear of falling, pain, mood, and grip strength. Information on barriers to and enablers of PA participation are also collected. Data on mortality and use of health services are collected from the national register. In this 6-month intervention, all participants are assessed in their homes at baseline and after three and six months, and at 12 months after randomization they will receive a follow-up questionnaire.

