### Sample size calculation

A priori sampled size calculations are based on previously published work [20] and on our pilot study conducted among 55 community-dwelling older people who were followed up for six months after discharge from hospital. In our pilot study, using an accelerometer, daily active time measured as mean amplitude deviation (MAD) above 0.0167 g was 250 ± 103 min. It has been estimated that a 20% increase in habitual physical activity, as measured by an accelerometer, in the intervention group compared to standard care control group will be clinically meaningful [21]. For this effect size, a significance level of 0.05 for the PA outcomes and a power of 80% will be set. Thus, the required sample size is 53 participants in each group. Assuming a dropout rate of 10–15%, 60 participants per group (total 120 participants) are required.

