### Measures

Baseline measurements start in the hospital ward and continue immediately after discharge to home. The 3- and 6-month assessments are performed in the participant’s home. Before the study start, examiners are given training in the testing procedures. At baseline, chronic conditions, use of prescription medication and the type of musculoskeletal condition that resulted in hospitalization (diagnosis) and its treatment (e.g. surgery type and medication) are drawn from the medical records of the Central Hospital of Central Finland and health center hospital. All the other measures and schedule are listed in Table 1.

**Table 1 Tab1:** Measures included in the study at each time-point

Intsrument	Domains	Time point					
		Prior to hospital admission	Baseline	3 months	6 months	12 months	Ref.
Main outcome measures							
Physical activity	Accelerometer 6 days		x	x	x	–	
	Diary of physical activity 6 days		x	x	x	–	
	Modified Grimby scale	x	x	x	x	x	[22, 23]
	YPAS (standing/walking & lying down/sitting)	x	x	x	x	x	[45]
	Unmet physical activity		x	x	x	x	[32]
Short Physical Performance Battery (SPPB)	Balance, 4 m walking, chair rising		x	x	x	–	[25]
Mobility disability	Moving outdoors	x	x	x	x	x	[46]
	Walking 500 m	x	x	x	x	x	[46]
	Walking 2 km	x	x	x	x	x	[46]
	Stair climbing	x	x	x	x	x	[46]
	Lifting (10 kg)	x	x	x	x	x	[46]
Self-rated mobility			x	x	x	x	
Secondary outcomes							
Life-Space Mobility (LSA)	Within home	x	x (modified)	x	x	x	[26]
	Outdoor	x	x (modified)	x	x	x	[26]
	Neighborhood	x	x (modified)	x	x	x	[26]
	Town	x	x (modified)	x	x	x	[26]
	Unlimited	x	x (modified)	x	x	x	[26]
Impact on Autonomy & Participation (IPA), 41 items		–	x	–	x	x	[27]
Fear of falling (FES-I), 16 items			x	x	x	x	[28]
History of falls			during preceding year	during preceding 3 months	during preceding 3 months	during preceding 6 months	
Depressive symptoms (CES-D), 20 items			x	x	x	x	[36]
Pain	Presence of musculoskeletal pain		x	x	x	x	[38]
	Pain Interference Subscale from the Brief Pain Inventory (BPI)		x	x	x	x	[29]
Maximal isometric grip strength			x			x	
Perceived environmental barriers	PENBOM		x	x^a^	x	x	[31]
	Home environment		x	x	x	x	[47]
Perceived environmental facilitators	PENFOM		x	x^a^	x	x	[31]
	Exercise facilities		x	x^a^	x	x	
	Home environment		x	x	x	x	
Barriers to physical activity	Barriers (BOPA)		x	x^a^	x	x	[30, 48]
	Avoidance of moving outdoors		x	x^a^	x	x	[48]
Health, Cognition & demographics							

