### Outcome measures of physical activity and mobility

The primary outcome of this study is PA and sedentary time measured with a 3-dimensional accelerometer (Hookie AM20 Activity Meter, Hookie Technologies Ltd., Espoo, Finland and UKK RM42, UKK Institute, Tampere, Finland). The accelerometer is attached on the non-affected anterior thigh line with a transparent, adhesive film as typically used in wound healing (Opsite Flexigrid, Smith&Nephew, United Kingdom). Data are collected over six consecutive days. In the analyses, the crude accelerometer data are used for calculating the parameter of interest. Sedentary behavior (time spent still without moving, MAD <0.0167 g) is assessed from the raw acceleration data based on intensity. The intensity of PA is calculated as one-minute ranges of movement measuring an average of MAD of the resultant acceleration and converted into metabolic equivalents (MET). Using METS, PA is classified into light, moderate and vigorous PA. MAD-based cut-points for light, moderate and vigorous locomotion against VO_2_ across a range of walking speeds are validated in our treadmill tests. In addition to accelerometer measurements, the participants keep PA diary on data collection days.

Level of PA over the previous month is assessed with the self-report scale by Grimby [22], which has been translated into Finnish and further modified and validated [23, 24]. The 7-point scale describes the level of PA as follows: 0) mostly resting, or lying down, 1) hardly any activity, mostly sitting, 2) light physical activity, such as light household tasks, 3) moderate physical activity for about 3 h a week: walking longer distances, cycling and domestic work, 4) moderate physical activity for at least 4 h a week or heavier physical activity 1–2 h a week, 5) heavier physical activity or moderate exercise for at least 3 h a week, and 6) competitive sports. Self-reported PA is assessed at 12 months in addition to the baseline, 3- and 6- month measurement points.

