#### Physical activity counseling

Goal Attainment Scaling (GAS) [40] is applied to set one or more PA-related goals. During the first visit, the method is presented to the participants. Their own goals and wishes are discussed to enable them to set goals based on the SMART principle (specific, measurable, achievable, realistic and time-based) [41].

Individual face-to-face PA counseling with a personalized PA plan takes place after three months in the participants’ homes. Motivational interviewing techniques will have been used during the counseling sessions to help participants to find inner motivation for adopting an active lifestyle, overcome barriers and detect sedentary behavior patterns. The topics covered during the session include the participant’s earlier and present PA level, the participant’s interest in returning to her or his previous activities, the possibility to starting a new type of PA or exercise, and guidance on how to be active in performing everyday chores. The problem-solving method is used to address perceived obstacles to PA. Participants are also given information on the PA courses and facilities offered by the municipality. To practice the exercise program, they are also given an opportunity to visit a gym or swimming pool with the physiotherapist.

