### Statistical analysis

All analyses will be performed using the intention-to-treat principle. Means, standard deviations and frequencies will be calculated for the demographic variables. Normality of the distributions will be tested. At baseline, the significance of differences between the intervention and control group will be tested by cross-tabulation and chi-square tests in the case of discrete variables, by Student’s t-test for independent samples for normally distributed data and by Mann-Whitney U-test for non-normally distributed continuous data. Associations between variables will be analyzed using Pearson’s correlation coefficient. The effects of the intervention will be assessed using repeated measures ANOVA, covariance analysis and linear mixed models. Generalized estimating equations (GEE) models will be used to analyze differences in changes in prevalence over three time points. The level of statistical significance will be set at *p* < 0.05 (two-sided). In all future publications, data will be reported following the criteria recommended by the CONSORT guidelines [42].

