The intervention is designed to increase PA, which might enhance patients’ personal life-space mobility and physical functioning. For this reason, the primary outcomes are PA and sedentary behavior measured by a 3D accelerometer and mobility measured using the SPPB. However, to gain detailed information on older persons’ life situations and participation in society after an acute medical challenge, other outcome measures are also important. To our knowledge, little is known on the effect of easily adoptable home-based rehabilitation programs on the PA of participants recently discharged from hospital after a musculoskeletal injury or surgery. In this time period specific patient groups have just initiated the recovery process, but are still weak and in need of assistance to complete their recovery. To contribute to meeting this need, we propose a home-based exercise program that may overcome some of the barriers to participation in rehabilitation, such as difficulties in using public transportation and lack of support for going outside the home without help. The intervention is supported by a physiotherapist regularly, as we consider that the home-visits during the follow-up period, will support patients to achieve their goals and succeed with the rehabilitation program designed together with them. Specially patients with cognitive problems or who have lack of motivation. This program might have potential to be integrated to the public health system and add value to the hospitals discharge protocol for the benefit of older people.

We are aware that it is challenging to run an intervention for older people who also suffer from multiple diseases and whose range of functional capacity is wide. Nevertheless, it is important to conduct a real-life study and develop an intervention that could also help promote daily PA and minimize mobility decline in older adults with low functional capacity. This project has the ability to bring out new practices regarding PA programs for older people after acute hospitalization due to musculoskeletal problems. We believe that the knowledge gained from this study will be of value to the scientific community and help in the development of rehabilitation strategies in hospitals, primary health care and the home environment among older people.

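### The Abstract, Methods and Discussion define the primary outcome differently, Table 1 adds a longer list, and only accelerometer active time is powered

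*Protocol article*

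**What the plan says.** The article describes the primary outcome in four places.

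- Abstract, Methods: "Primary outcomes are PA measured using a 3-dimentional accelerometer, and mobility assessed by the Short Physical Performance Battery and self-reports".
- Outcome measures of physical activity and mobility: "The primary outcome of this study is PA and sedentary time measured with a 3-dimensional accelerometer". The same section goes on to describe the SPPB and self-reported mobility but does not call them primary.
- Discussion: "the primary outcomes are PA and sedentary behavior measured by a 3D accelerometer and mobility measured using the SPPB". Self-reports are not mentioned.
- Table 1: 12 rows stand under the heading "Main outcome measures", apart from the block of secondary outcomes.

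Two other passages bear on the point. The sample size section rests on one variable, "daily active time measured as mean amplitude deviation (MAD) above 0.0167 g was 250 ± 103 min", and sets "a significance level of 0.05 for the PA outcomes and a power of 80% will be set". The Statistical analysis section gives one general threshold: "The level of statistical significance will be set at *p* < 0.05 (two-sided".

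**The concern.** The statements disagree on substance. The SPPB is primary in the Abstract and the Discussion but is not given that rank where the Methods name a single primary outcome. Self-reported mobility is primary in the Abstract and absent from the Discussion's list. Its content also varies: the text lists four mobility tasks, while Table 1 lists five, adding lifting 10 kg.

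Two things are at stake. A primary outcome chosen among these versions after the data are seen could not be told apart from selection by result. And if several of the outcomes were treated as primary at the full 0.05 each, with any one sufficient, the overall error rate would exceed the stated 5%. The Abstract ties possible uptake of the program by the health care system to positive effects without saying on which outcome.

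**Working it through.** **1. The definitions side by side.**

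| Place | Accelerometer activity | Sedentary time | SPPB | Self-reports |
|---|---|---|---|---|
| Abstract | primary | not named | primary | primary |
| Methods, outcome section | primary | primary | described, not ranked | described, not ranked |
| Discussion | primary | primary | primary | not named |
| Table 1 | main | no row of its own under accelerometry | main | main (10 rows) |

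Table 1 count: five activity rows (accelerometer, diary, Grimby, YPAS, unmet activity), the SPPB, five mobility tasks and self-rated mobility, so 5 + 1 + 5 + 1 = 12.

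**2. The plan's own figure.** Inputs from the sample size section: mean 250 min, SD 103 min, 20% increase, 80% power, level 0.05. The difference is 0.20 × 250 = 50 min. With n per group = 2 × [SD × (z for the level + z for power) / difference]²:

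- One-sided 0.05: 2 × [103 × (1.645 + 0.842) / 50]² = 52.5, so 53, the stated figure.
- Two-sided 0.05: 2 × [103 × (1.960 + 0.842) / 50]² = 66.6, so 67.

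The stated 53 also follows from a two-sided covariance analysis with an unstated baseline correlation of about 0.46, since 67 × (1 − 0.46²) = 52.8. Sidedness is a separate matter. What counts here is that the calculation spends the whole 0.05 once, on active time, and leaves nothing for a second primary outcome.

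**3. Chance of at least one false positive if the program has no effect and any one outcome suffices.** For k independent outcomes this is 1 − 0.95^k counting both directions, and 1 − 0.975^k counting only results in the program's favor. The 0.5 columns come from simulating test statistics with a common correlation of 0.5 (400,000 draws). That correlation is assumed, as the article gives none.

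| k | Both directions, independent | Both directions, 0.5 | Favorable only, independent | Favorable only, 0.5 |
|---|---|---|---|---|
| 2 | 9.8% | 9.1% | 4.9% | 4.6% |
| 3 | 14.3% | 12.6% | 7.3% | 6.3% |
| 12 | 46.0% | 31.9% | 26.2% | 15.9% |

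The reference rates are 5% for both directions and 2.5% for the favorable direction. For 12 outcomes counting both directions, assumed correlations of 0.3, 0.7 and 0.9 give 40%, 23% and 14%. Positive correlation lowers the rate, so the independent columns are upper bounds.

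**4. What it would cost to keep several primaries with a Bonferroni split.** Power for active time with 53 per group is Φ(50 / [103 × √(2/53)] − z) = Φ(2.50 − z), two-sided and without baseline adjustment:

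| Primaries | Level for each | Power with 53 per group | n per group for 80%, before dropout |
|---|---|---|---|
| 1 | 0.05 | 70.5% | 67 |
| 2 | 0.025 | 60% | 81 |
| 3 | 0.0167 | 54% | 89 |
| 12 | 0.00417 | 36% | 117 |

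**The case against.** The strongest reply is that this is a journal article. A multiplicity rule, a success rule and a primary visit are commonly left to the full protocol or the analysis plan, and neither is shown. That stands: their absence is not the error. It does not answer the point, because no unseen document makes conflicting statements in this one agree.

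The conflict is also partly nested. The Methods put accelerometry, the SPPB and self-reported mobility under one heading, apart from the secondary outcomes, which is close to the Abstract and Table 1. The sentence naming one primary outcome and the Discussion's shorter list still do not fit with it.

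Several stronger readings are tempting but unsupported:

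- A reader might infer that significance on any one of 12 measures would be declared a positive trial. No section says so. The Statistical analysis section sets a general threshold and does not promise a confirmatory test for each row. Nothing excludes that reading either, so it can only be put as a conditional.
- The count of 12 rests on the heading in Table 1 alone. The diary is introduced only as a supplement to accelerometry. Active and sedentary time share the 0.0167 g cut-point and are largely mirror images, so the Discussion's list amounts to two or three outcomes.
- The 46% counts both directions. A claim of benefit needs a favorable result, for which the figure is 26%.
- A reader might double the count for the 3- and 6-month visits. Separate tests at each visit are not stated, and the named methods include repeated-measures and mixed models that can use the visits jointly.
- A reader might take "Individual face-to-face PA counseling with a personalized PA plan takes place after three months" to mean that counseling occurs only then, and choose 6 months for that reason. Table 2 lists counseling from week 2, and goal setting under the counseling section starts at the first visit.

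Timing also matters. The trial was registered in January 2016, recruitment was due to end by August 2017, and the article appeared in November 2017. Naming a primary outcome without checking it against the registered one could itself be a late outcome change. That stands and shapes the fix.

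**Conclusion.** The point holds as an internal contradiction: the definitions of the primary outcome cannot all be true, and the article does not let a reader decide between them. Only active time is powered.

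The effect on the error rate is conditional on more than one outcome being primary and any one being enough. On the narrower readings, two or three outcomes, the two-sided rate is at most about 10% or 14% instead of 5%. Taking all 12 rows of Table 1 as primary gives an upper bound of 46%, or about 32% at an assumed correlation of 0.5. Counting only results that favor the program, these become 26% and 16% against 2.5%. The documents do not establish that the trial will be judged this way.

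**What to change.** Reconcile the Abstract, the outcome section, Table 1, the Statistical analysis section and the Discussion to one definition. It should agree with the registered outcome and be settled, with a date, before outcome data are examined.

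The natural choice is:

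- Primary: accelerometer daily active time (MAD above 0.0167 g, the powered variable) at 6 months. This is the end of the intervention and, by Table 1, the last visit with accelerometry and the SPPB.
- Second in fixed sequence: the SPPB at 6 months, tested at two-sided 0.05 only if active time is significant.
- Secondary, with confidence intervals and no confirmatory claim: sedentary time, self-reported activity and self-reported mobility.

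If the registered outcome differs from this, the difference should be stated and explained.

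The cost is mainly wording, plus the check against the registration. The fixed sequence keeps the error rate at 5% for the two tests, needs no alpha split and adds no participants on account of multiplicity. The downside is that the SPPB cannot be claimed as confirmatory if active time fails. Other schemes that control the error rate would also do, but an alpha split has the power cost shown above.

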**Discussion:**

This study investigates the effects of a rehabilitation program on PA and mobility among older people at risk for increased sedentary time and mobility problems. If positive effects are observed, the program can be considered for incorporation into the health care system and thereby contribute to the rehabilitation of older people who have recently been discharged from hospital.

**Trial registration:**

ISRCTN13461584. Registered 27 January 2016.

## Background

Twenty percent of people in Finland are aged 65 years or over, and many of them have been hospitalized because of an acute or chronic musculoskeletal injury or disorder. During and after hospitalization, older people often experience a substantial decline in function; this can result in loss of independence in daily life, decreased quality of life, and thus increased likelihood of readmission to hospital or even to moving from home into a long-term care facility [1–3]. For example, up to half of hip fracture patients do not achieve their pre-fracture level of mobility, or regain independence in daily life [4–6]. The regaining of mobility during and after hospitalization is crucial for enabling old people to move around inside and outside the home, maintain physical activity (PA), re-engage in social activity and preserve their autonomy. Indeed, adequate mobility is a key component of functional recovery and participation in society [7].

Whereas physical activity includes household tasks, activities of daily living, exercise and sports [8], sedentary behavior refers to any waking behavior characterized by an energy expenditure of ≤1.5 metabolic equivalents (METs) while in a sitting, reclining or lying posture [9]. Sedentary behavior is common, particularly among older people who have been hospitalized. Typically, sedentary time exceeds 20 h per day among those admitted to hospital [3] and older patients walk only an average of 700 to 1500 steps per day [10–12]. Obviously, patients who have had an orthopedic surgery are even less active during hospitalization than those who have not been treated surgically [13, 14]. Little information is available on the physical activity level of older people after discharge from hospital. As a patient’s mobility limitations persist long after discharge to home [5, 15, 16], it is likely that their amount of physical activity will also be insufficient for months. Sedentary behavior, in turn, increases the risk for future injury and subsequent hospitalization. Thus, optimizing recovery by promoting PA and improving mobility after a musculoskeletal injury or disorder in the lower limbs or back has the potential to reduce the burden on individuals and society.

Currently, little evidence exists on the best ways to promote PA and support mobility recovery after hospitalization among older people with musculoskeletal injury or disorder. Although there is no consensus on rehabilitation best practices, recent home-based rehabilitation interventions with minimal contact from a physiotherapist (4 to 5 visits) boosted by telephone calls resulted in improvement in the physical function of the lower limbs [17] self-reported mobility [18] and self-reported level of PA [19] among hip fracture patients.

The present study, investigates the effect of a six-month individually tailored and home-based counseling and rehabilitation program in comparison to standard care on PA and mobility recovery among community-dwelling men and women aged 60 years or older who have been recently discharged from hospital and are recovering from a musculoskeletal injury or lower limb or back disorder. Objective measures of PA using 3D accelerometers are utilized to assess sedentary time and the duration and intensity of PA. This will especially help detection of nuances in light activity during recovery after acute hospital stay among older people with musculoskeletal problems. This article describes the recruitment process, data collection, and intervention of this ongoing randomized controlled trial.

